#### ***Total body dual-energy X-ray absorptiometry scan***

The ratio of total body fat (g) to lean body mass (g) will be measured using dual-energy X-ray absorptiometry (DXA) on a GE-Lunar Prodigy machine (GE LunarCorp, Maddison, WI) equipped with adult property software, version 3.6, which is appropriate for body weight of subjects 8–18 years. Fast scan mode and standard subject positioning will be used for these measurements. Mean precision of our machine is 1.3% for soft tissue.

#### ***Assessment of energy intake and diet quality***

The Australian Child and Adolescent Eating Survey (ACAES – version 1.2) [49] is a food frequency questionnaire based on the previous 3–6 months of food intake across all food categories. It will be interviewer-administered by the same dietitian at each assessment. At baseline, the ACAES will calculate the dietary intake over the previous 6 months. At subsequent assessments (3, 6 and 12 months) the ACAES questionnaire will calculate the dietary intake since the previous assessment. The ACAES will determine total caloric intake and macro and micronutrient content of the participant’s diet.

### Assessment of energy expenditure

Daily energy expenditure will be measured at 0, 3, 6 and 12 months. This will be assessed with the use of a SenseWear MF (Mini Form factor) device (analysed with SenseWear Software Version 7.0. Temple Healthcare Pty Ltd, Bowral, Australia) which is an external armband worn in this study for 5 days before each assessment time point. Based on measurements of accelerometry, heat flux, galvanic skin response, skin temperature, near-body temperature and patient characteristics (gender, age, height, weight) proprietary algorithms will calculate energy expenditure, number of steps taken and sleep duration.

### Monitoring of safety and adverse events

#### ***Blood glucose management during study***

All subjects will receive 2 weekly telephone review of blood glucose control for the first 3 months and monthly thereafter. They will also have access to a 24 hour phone hotline serviced by one of 4 paediatric endocrinologists for acute insulin dose adjustment.

#### ***Compliance assessment***

Assessment of adherence to the study medication regimen will be assessed at each assessment time point (3 months, 6 months and 12 months). All unused study drugs will be returned to the investigator for counting. MEMS caps (AARDEX group LTD, Sion, Switzerland) will also be utilised to measure compliance. These caps record how many times the study medication bottle is opened between study visits and the data will be downloaded for review and analysis. Compliance will be encouraged at the 3 month and 6 month study visit using the downloaded data from the MEMS cap.

### Monitoring of adverse events

Renal, liver function tests and lactate will be performed at 0, 3, 6 and 12 months. Metformin can decrease levels of vitamin B12, so children with vitamin B12 deficiency will be excluded and vitamin B12 will be monitored during the study. The risk of hypoglycaemia will be monitored and insulin will be adjusted accordingly.

Metformin can cause nausea and diarrhoea. Any illness or need for additional medication in a subject will be recorded throughout the study. Letters to the subjects’ endocrinologists and general practitioner advising of entry into the trial will be sent, and the WCH and FMC emergency departments will have a record of the subject’s participation in the trial in the medical records.

All adverse events will be reported to the medication safety committee for the trial in a monthly monitoring update. All serious adverse events will be reported to the medication safety committee and the WCH human research ethics committee within 24 hours of the event occurring. Serious adverse events occuring in FMC participants will also be reported to the FMC human research ethics committee. A serious adverse event is defined as one which is fatal or life threatening or requires hospitalization.

### Data analysis

All analyses will be performed under the intention to treat principle. The primary outcome, FMD, will be compared between metformin and placebo groups over 12 months using a linear mixed effects model. Linear mixed effects models will also be used to compare changes in secondary continuous outcomes (GTN, adiponectin/leptin ratio, lipids, HbA1c, insulin requirements, cIMT and aIMT) between treatment groups (metformin/placebo) over the four reviews. The linear mixed effects models will account for the within-subject correlations that are produced when repeating outcome measurements in individual subjects over time. Both unadjusted and adjusted analyses will be performed, with adjustment for important pre-specified baseline covariates including age, sex and BMI.

While no studies have looked at the effect of metformin on FMD in T1D in this age group, our previous work found an improvement in FMD of 3.1% with an SD of 4.3 in children with T1D receiving folic acid over 8 weeks [46,47]. Assuming an equivalent improvement with metformin from baseline to 12 months, we would require 32 subjects per group to have 80% power to detect a difference in FMD changes of 3.1% between randomised groups (alpha = 0.05 two-sided). Our dropout rate in previous studies in this population with similar intervention and investigation over 24 weeks has been 1–2%. We have conservatively factored in a dropout rate of 15% giving a total recruitment required of 76 subjects (38 in each group).

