**Methods/Design:**

This study is a 12 month, double blind, randomised, placebo controlled trial to determine the effect of metformin on vascular health in children (age 8–18) with T1D. The sample size is 76 with 38 children in the metformin group and 38 children in the placebo group. Vascular health and biochemical markers will be measured at baseline, 3, 6 and 12 months. Vascular function will be measured using flow mediated dilatation and glyceryl trinitrate mediated dilatation of the brachial artery and vascular structure will be measured with carotid and aortic intima media thickness, using standardised protocols.

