#### ***Vascular structure***

The thickness of the intima and media layer of the carotid (cIMT) and aortic (aIMT) walls are structural markers of atherosclerosis and can be evaluated by ultrasound.

cIMT is a well-established index of early atherosclerosis that correlates with prevalent and incident coronary heart disease and stroke [26]. Relative risk of stroke or myocardial infarction in older adults without a history of cardiovascular disease increases by 35% with an increase in cIMT of 1 SD, i.e. a relatively large clinical effect for a small change in cIMT [26]. Overweight and obese children have increased cIMT compared with age matched controls [27]. cIMT has been used as a primary outcome measure in landmark intervention trials [7,28]. Diet and exercise improve endothelial dysfunction and reduce cIMT in obese children over 12 months [29]. In this study FMD improved early and was maintained and cIMT improved at 12 months. Atherosclerosis begins in the abdominal aorta. We and others have shown that aIMT precedes changes in cIMT in children with accelerated atherosclerosis, including T1D [3,4]. cIMT and aIMT will be used in this study as structural outcome measures.

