### Outcome measures

Table 1 shows which primary and secondary outcomes will be measured at different time points in the study. Table 2 shows additional information which will be collected at the assessments and Table 3 shows the additional information collected at each telephone call (which occurs 2 weekly for the first 3 months and monthly thereafter).

**Table 1 T1:** Primary and secondary outcome measures

	**Baseline**	**3 months**	**6 months**	**12 months**

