**Secondary outcomes**				
Vascular smooth muscle function (GTN)	*	*	*	*
Vascular structure (cIMT and aIMT)	*			*
Physical examination	*	*	*	*
- anthropometric measurements (height, weight, BMI, waist circumference)				
- the presence of acanthosis nigricans				
- severity of acne				
- ferriman - gallwey score (girls)				
Frequency and severity of hypoglycaemia	*	*	*	*
Insulin dose (units/kg/day)	*	*	*	*
Glycosylated haemoglobin	*	*	*	*
Fasting glucose	*	*	*	*
Fasting total/HDL/LDL cholesterol/triglycerides	*	*	*	*
High sensitivity C-Reactive Protein (HsCRP)	*	*	*	*
Early morning urinary albumin/creatinine	*	*	*	*
Urinary prostaglandin F2α	*	*	*	*
Liver function, renal function tests and lactate	*	*	*	*
Total Plasma homocysteine	*	*	*	*
Girls only: Testosterone, free androgen index, Sex Hormone-Binding Globulin, Dehydroepiandrosterone, Anti-Mullerian Hormone, 17-hydroxy progesterone, prolactin, Luteinizing hormone, Follicle Stimulating Hormone, progesterone & oestradiol	*	*	*	*
Total Adiponectin	*	*	*	*
Leptin	*	*	*	*
Body composition (bio-electrical impedance analysis using Tanita body composition scales)	*	*	*	*
Retinal photograph	*			*
Total body Dual-energy X-ray absorptiometry scan	*			*

*Indicates assessment of a variable at the timepoint indicated.

**Table 2 T2:** Additional information collected at assessments

	**Baseline**	**3 months**	**6 months**	**12 months**
ACAES questionnaire v1.2	*	*	*	*
Physical examination – tanner stage	*	*	*	*
Daily energy expenditure (SenseWear arm band)	*	*	*	*
Family history of premature cardiovascular disease	*			*
Pregnancy test in post menarchal girls	*	*	*	*
Serum cotinine	*	*	*	*
Adherence data using MEMS caps and manual tablet count	*	*	*	*
Serum Vitamin B12, Folate, red cell folate	*	*	*	*

* Indicates assessment of a variable at the timepoint indicated.

**Table 3 T3:** Additional information collected with each phone call

	**0-3 months**	**3-12 months**
Side effects	2 weekly telephone calls	Monthly telephone calls
- hypoglycaemia (number, severity)		
- gastrointestinal symptoms (nausea, vomiting, diarrhoea, anorexia)		
- rash		
- other side effects		
Insulin requirements		

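### cIMT and aIMT are to be compared over four reviews, but Table 1 schedules them only at baseline and 12 months, so the 3- and 6-month comparisons cannot be estimated

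*Protocol article*

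**What the plan says.** Three places in the protocol article bear on when and how the structural outcomes are measured and compared.

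- **Data analysis.** Linear mixed effects models are to compare changes in the secondary continuous outcomes. The list begins with GTN and ends with "insulin requirements, cIMT and aIMT) between treatment groups (metformin/placebo) over the four reviews". The section adds: "The linear mixed effects models will account for the within-subject correlations that are produced when repeating outcome measurements in individual subjects over time". Unadjusted and adjusted analyses are planned; the covariates named are age, sex and BMI, in an open list.
- **Table 1.** The Outcome measures section sends the reader here for timing: "Table 1 shows which primary and secondary outcomes will be measured at different time points in the study". The columns are baseline, 3, 6 and 12 months. The row "Vascular structure (cIMT and aIMT") is marked at baseline and 12 months and is empty at 3 and 6. The row above it, "Vascular smooth muscle function (GTN"), is marked at all four.
- **Abstract, Methods/Design.** "Vascular health and biochemical markers will be measured at baseline, 3, 6 and 12 months". The next sentence counts carotid and aortic intima media thickness among the vascular measures and makes no exception for their timing.

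The Background, under Vascular structure, gives these measures their role: "cIMT and aIMT will be used in this study as structural outcome measures". Both are named in the secondary objectives.

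**The concern.** The analysis sentence assumes four measurements of each structural outcome, and the schedule supplies two. The article states this analysis and names these outcomes, so this is an inconsistency in the text and not a detail left to an analysis plan.

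cIMT and aIMT are the trial's only measures of vascular structure. If the mismatch stands, the analyst must decide later what the comparison is: a change score, a 12-month value adjusted for baseline, or a constrained mixed model. These can differ in precision, and a choice made once the data are in hand is open to challenge. A reader of the abstract and the Data analysis section would also expect structural results at 3 and 6 months that the trial will not have.

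**Working it through.** **1. The plan's own figure.** The only computed figure is the sample size for FMD. Inputs from Data analysis: difference 3.1, SD 4.3, two-sided alpha 0.05, power 80%, dropout 15%.

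- Normal approximation: n = 2 × (1.96 + 0.84)² × 4.3² / 3.1², which rounds up to 31 per group.
- t-test version: 31.2, rounded up to 32 per group, as stated.
- Dropout: 32 / 0.85 = 37.6, rounded up to 38 per group, 76 in total, as stated.

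The figure reproduces. It concerns FMD only, so nothing below changes it.

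**2. Schedule against analysis list.**

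| Outcome in the mixed-model list | Visits marked in Table 1 |
|---|---|
| GTN, lipids, HbA1c, insulin dose, adiponectin and leptin | 0, 3, 6, 12 months |
| cIMT, aIMT | 0, 12 months |

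Only the two structural outcomes fail to fit. The empty cells do not look like a fault of text extraction: the retinal photograph and DXA rows show the same two marks.

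**3. What can be estimated.** Take visit as a category.

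- Four visits × two arms = 8 fixed-effect parameters.
- Data at 0 and 12 months only: two visits × two arms = 4 distinct design rows. A check of the design matrix gave rank 4 against 8 columns.
- The 4 parameters that involve 3 and 6 months therefore have no data behind them.

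**4. What the two-visit mixed model gives.** With 4 fixed effects (intercept, arm, visit, arm by visit) and a random intercept, the model can be fitted. On simulated complete data for 76 children (simulation values assumed) it converged. Its arm-by-visit term was −0.494 with SE 0.178. The plain difference in mean change was also −0.494 with SE 0.178. With no constraint at baseline, the mixed model is the change-score comparison.

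**5. Precision compared with baseline adjustment.** Assume the same variance σ² at both visits and in both arms, and a correlation r between baseline and 12 months. Per child:

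- change score: 2σ²(1 − r)
- 12-month value adjusted for baseline: σ²(1 − r²)
- ratio, adjusted to change: (1 + r)/2
- reduction in variance: 1 − (1 + r)/2 = (1 − r)/2

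| Assumed r | Reduction in variance |
|---|---|
| 0.3 | 35% |
| 0.5 | 25% |
| 0.7 | 15% |
| 0.9 | 5% |

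The article gives no baseline to 12-month correlation for intima media thickness. The intra-class coefficients of 0.97 and 0.99 under the ultrasound methods describe agreement between and within observers and do not supply r.

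**The case against.** The strongest reply is that this is loose wording. The phrase about four reviews closes a shared list in which every other outcome does have four visits, and Table 1, to which the text refers for timing, is unambiguous. The abstract is a one-sentence summary. The planned method is a mixed model of change, and two visits are enough to fit one. All of this stands, and it limits the point to a mismatch between text and schedule.

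Three stronger readings are tempting, and the article does not support them.

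- *The analysis of cIMT and aIMT cannot be done.* A reader might infer this from the rank count. But only the 3- and 6-month contrasts and the shape of the time course are lost; the 12-month difference in change can be estimated.
- *The plan wastes up to 35% in variance.* That figure requires a low correlation and a model without a common baseline mean. The article does not say how baseline enters the model, its covariate list is open, and such detail is commonly left to an analysis plan. With a common baseline mean, the loss essentially disappears. The percentages show what is at stake in the choice; they do not measure the mismatch itself.
- *DXA has the same defect.* It is also measured twice, but it is not in the list of outcomes to be modelled, so nothing is contradicted there.

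It is also fair to say that changing the time points alone would cure the contradiction. Baseline adjustment is a further step, recommended because the corrected sentence must state some comparison, and this one uses a value already collected.

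**Conclusion.** The point holds for cIMT and aIMT. The four-review comparison stated for them is impossible under Table 1: two of four visits carry no data, and 4 of 8 treatment-by-visit parameters cannot be estimated. What remains is a single contrast at 12 months. Under the assumptions of equal variances and an unconstrained baseline, adjusting that contrast for baseline would reduce its variance by 5% to 35% for r between 0.9 and 0.3. No r is documented, so this range is illustrative.

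The rank result treats visit as a category. If time were instead entered as a straight line, a model could be fitted, but its slope would be only the 12-month change divided by 12 and still no comparison over four reviews.

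The article does not say outright which schedule was intended. The two-mark row, shared with the retinal photograph and DXA, points to Table 1 as deliberate. Two secondary outcomes are affected; the primary FMD analysis, the 38 per group and the power are not.

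**What to change.** 1. In Data analysis, take cIMT and aIMT out of the sentence on four reviews.
2. Add a sentence to this effect: cIMT and aIMT are compared between groups at 12 months with adjustment for the baseline value of the same measure, by ANCOVA or, equivalently, a two-visit mixed model with a common baseline mean; age, sex and BMI are added in the adjusted analysis.
3. In the abstract, say that vascular function is measured at baseline, 3, 6 and 12 months and vascular structure at baseline and 12 months.
4. If four scans of vascular structure were in fact intended, correct Table 1 instead and leave the other two places as they are.

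Steps 1 to 3 cost wording only: no added scans, no change in sample size. They should be settled before unblinding. Step 4 would mean two further scans of vascular structure per child, at 3 and 6 months, beyond what Table 1 now shows.

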## Discussion

Cardiovascular disease is the commonest cause of morbidity and mortality in T1D. The origins of cardiovascular disease are in childhood. Good metabolic control is essential in the prevention of cardiovascular disease however targets for optimal glycaemic control are often not met in children and adolescents with T1D. It is crucial to investigate additional effective and early interventions to prevent or reduce vascular pathology in this population. Metformin is a good candidate for early prevention of cardiovascular disease as it has been prescribed in youth with T2D for over 10 years and reduces cardiovascular disease in T2D.

Metformin is generally well tolerated and easy to administer with a good safety profile. Vascular health outcomes will be measured using non invasive, valid and reliable measurements by experienced investigators. This is, to our knowledge, the first study to examine whether administration of metformin will improve vascular health in children with T1D. Determining the effect of metformin on vascular health in children with T1D will provide a potential early intervention for cardiovascular disease in this population.

## Abbreviations

ACAES: Australian child and adolescent eating survey; aIMT: Aortic intima media thickness; AMPK: AMP activated protein kinase; BMI: Body mass index; cIMT: Carotid intima media thickness; CSII: Continuous subcutaneous insulin infusion; DXA: Dual-energy X-ray absorpitometry; FMC: Flinders Medical Centre; FMD: Flow mediated dilatation; GTN: GTN mediated dilatation; HbA1c: Glycosylated haemoglobin; IMT: Intima media thickness; T1D: Type 1 diabetes; T2D: Type 2 diabetes; WCH: Women’s and Children’s Hospital.
